### 3.6. Statistical Analysis

#### 3.6.1. Sample Size

Current literature on the potential effect of telemonitoring platforms on outcomes such as quality of life is scarce. However, based on previous reports [40,41], it has been estimated that a total of 80 participants (40 per arm) will be necessary to achieve 80% statistical power at standard significance levels (5% alpha two-tailed), assuming an intergroup difference in EQ-5D questionnaire means of 0.1 point, a symmetric standard deviation between groups of 0.35 points, a strength of linear correlation between measurements of 0.7 (r = 0.7), and 3 instances of measurement for both groups.

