#### 3.6.2. Analysis Strategy

For the statistical analysis, means, medians, standard deviations, interquartile ranges, ranges, and absolute and relative frequencies will be used for descriptive analysis. Inferential analysis will employ Student’s *t*-test or the Mann–Whitney U test for comparing means based on data distribution and variances, and Fisher’s Exact Test for evaluating categorical variables. The primary outcome will be evaluated in relation to the change in EQ-5D score means associated with their corresponding standard deviations through a repeated measures analysis of variance (ANOVA). Confidence intervals at 95% will also be constructed from the standard deviations of the mean changes to estimate the magnitude of the intervention effect among these patients. Additionally, the potential association between the implemented intervention and the development of categorical outcomes will be quantified using the relative risk statistic associated with their corresponding 95% confidence intervals. Subgroup analysis has not been considered in this study.

If an imbalance in participant characteristics is detected, confounding will be controlled using multivariable linear regression analyses. Model assumptions will be assessed graphically and by an evaluation of residuals. Heteroskedasticity will be addressed using the Cook–Weisberg method. All analyses will be conducted by a statistician unaware of the participants’ treatment assignment, following the intention-to-treat principle, and using Stata v.16.0^®^ software (StataCorp LP, StataCorp LLC., College Station, TX, USA, 1996–2020).

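### Section 3.6.2 offers a diagnostic test as the remedy for heteroskedasticity and a rank test as a comparison of means; the effect is modest and lies outside the primary ANOVA

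*Protocol article*

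**What the plan says.** All of this is in the Protocol article, section 3.6.2 (Analysis Strategy).

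- **Two-group comparisons.** Student's t-test is offered alongside the "Mann–Whitney U test for comparing means based on data distribution and variances". The sentence is general and does not list the variables it applies to.
- **Primary outcome.** Change in EQ-5D goes to a repeated measures ANOVA, and "Confidence intervals at 95% will also be constructed from the standard deviations of the mean changes".
- **Adjusted analysis.** "If an imbalance in participant characteristics is detected, confounding will be controlled using multivariable linear regression analyses".
- **Model checking.** "Model assumptions will be assessed graphically and by an evaluation of residuals".
- **Unequal variance.** A separate sentence then says "Heteroskedasticity will be addressed using the Cook–Weisberg method".

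The section names no robust standard errors, weighting, transformation or unequal-variance t-test.

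**The concern.** Two methods are given tasks that they cannot do.

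First, Cook–Weisberg is a score test of whether the residual variance is constant. Its output is a test statistic and a p-value. The coefficients, standard errors and intervals are the same after it as before. Checking of assumptions already has its own sentence, so the next sentence reads as the remedy, and the method it names is not one.

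Second, the null hypothesis of Mann–Whitney concerns the ordering of two distributions. It coincides with equality of means only when the arms differ by a pure shift. Variances are also given as a ground for choosing between the two tests. Yet Student's t pools the variance, and Mann–Whitney is itself sensitive to differences in spread and shape. Because the choice follows the observed data with no stated rule, the quantity tested is not fixed in advance.

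At stake is the validity of p-values and intervals in the secondary two-group comparisons and in the adjusted model. EQ-5D is a bounded score, so skewness and unequal spread are plausible.

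**Working it through.** No figure in the plan states the operating characteristics of these tests, so there is none to reproduce. The planned size is 80 in total, 40 per arm, with a common SD of 0.35 (section 3.6.1) and 1:1 allocation (section 3.2). All unequal arm sizes, unequal SDs and distribution shapes below are assumptions chosen to show a range.

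**1. Student's t with unequal variances.** Compare the true variance of the mean difference, V = s1²/n1 + s2²/n2, with the variance that the pooled test uses on average, P = sp²(1/n1 + 1/n2), where sp² = [(n1−1)s1² + (n2−1)s2²]/(n1+n2−2).

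*Arms 38/30, SDs 0.25/0.45 (larger SD in the smaller arm):*
- V = 0.0625/38 + 0.2025/30 = 0.00839
- sp² = (37×0.0625 + 29×0.2025)/66 = 0.1240, so P = 0.1240 × 0.05965 = 0.00740
- V/P = 1.135, with square root 1.065. The critical value 1.997 acts like 1.997/1.065 = 1.874, which gives about 6.5% on 66 degrees of freedom.

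*The same arms with the SDs swapped:*
- V = 0.2025/38 + 0.0625/30 = 0.00741
- sp² = (37×0.2025 + 29×0.0625)/66 = 0.1410, so P = 0.00841
- V/P = 0.881, with square root 0.939. The effective critical value is 2.127, which gives about 3.7%.

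*Arms 40/40:* V = P exactly, so there is no distortion to this order.

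Simulation agrees:

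| Arms | SDs | Student's t | Welch |
|---|---|---|---|
| 38/30 | 0.25/0.45 | 6.6–6.7% | 4.9–5.0% |
| 38/30 | 0.45/0.25 | 3.5–3.8% | 5.0% |
| 40/40 | 0.25/0.45 | 5.0–5.1% | 4.8–5.0% |

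**2. Does running Cook–Weisberg change anything?** Simulated regression of the outcome on arm and one covariate, no arm effect, 3,000 runs each:

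| Arms | SDs | Flagged by Cook–Weisberg | Ordinary least squares | HC3 |
|---|---|---|---|---|
| 30/40 | 0.5/0.25 | 95% | 6.9% | 5.1% |
| 40/40 | 0.2/0.5 | 99.8% | 4.8% | 4.6% |

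The test finds the problem almost every time, but finding it does not move the error rate. In the first row only the robust standard error does.

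**3. Does Mann–Whitney compare means?** Equal true means, 40 per arm, 5,000 runs each:

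| Shapes | Mann–Whitney | Student's t |
|---|---|---|
| Normal, SD 0.2 and 0.5 | 6.0% | 5.0% |
| Left-skewed and normal, both SD 0.35 | 9.3% | 5.4% |
| Opposite skews, both SD 0.35 | 31% | 5.9% |

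When both arms had the same distribution, Mann–Whitney rejected in 4.6% of runs. The higher rates therefore come from a difference in shape that the test is entitled to detect. They show that it answers a different question from a test of means.

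**The case against.** The strongest reply is that none of this reaches the primary result. EQ-5D change is analysed by repeated measures ANOVA, and confidence intervals for mean changes are planned whichever two-group test is picked. An estimate to set beside the 0.1-point difference assumed in section 3.6.1 will therefore exist. The regression is run only if imbalance is detected. This stands, and it limits the point to the two-group comparisons and the conditional adjusted model.

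Second, the plan has 1:1 allocation and a common SD, and nothing in it predicts arms of 38 and 30. This also stands. Inflation needs unequal arms with the larger SD in the smaller one, and the direction can reverse.

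Third, the wording may be loose for 'tested', with the remedy left to an analysis plan that is not shown. This stands only in part. Silence about a remedy would be no finding in a condensed article. But the text is not silent: it names a method as the remedy, and that method cannot be one. A later document would have to replace the sentence.

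Fourth, choosing between t and Mann–Whitney by distribution is common, and the statistician is blinded to allocation. Blinding limits a choice that favours an arm. It does not make the two tests address the same quantity, and it does not make either suitable for unequal variances.

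A reader might go further and infer that Mann–Whitney would give grossly false positives here. With 60% of one arm at the ceiling of the scale and equal means, it can reject in 31% to 49% of runs. The documents do not support that inference. The shape is extreme and assumed (with 30% at the ceiling the rate is 6% to 11%), and the two arms then truly differ in distribution. This is a difference of estimand, not type I error when the app has no effect.

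**Conclusion.** The point holds in a limited form. Section 3.6.2 wrongly presents a diagnostic test as a remedy and a rank test as a comparison of means, and it uses variances to choose between two tests that both fail to handle unequal variances. These are rules stated incorrectly, not details left out.

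The consequence is modest. For Student's t, type I error moves from 5% to about 6.6% or to below 4%, depending on which arm has the larger SD. Ordinary least squares reaches about 6.9% in one unfavourable setting. With equal arms the distortion disappears. All these figures rest on assumed drop-out and SDs. A reader might also infer that heteroskedasticity would invalidate the main result, but these sentences do not govern the primary ANOVA or its intervals. The correction is worth making because it is nearly free and is best settled before the data are seen.

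**What to change.** Replace the heteroskedasticity sentence with wording such as: *Regression models will use robust standard errors (HC3, or clustered by patient where measurements are repeated); the Cook–Weisberg test may be reported as a diagnostic only.*

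Replace the two-group sentence with wording such as: *Means will be compared with Welch's t-test, or with the adjusted model, whatever the observed distribution; Mann–Whitney will be reported as a supplementary rank-based comparison and not as a test of means.*

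Other mean-based choices would also be valid. What matters is that the method is fixed beforehand and that each test is described by what it tests.

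The cost is a few sentences of text and standard options in Stata, which the plan already names. The statistical price is a very small loss of precision when the variances are in fact equal. The sample size and the primary analysis are unaffected.

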## 4. Research Ethics

This study has undergone ethical evaluation by the Research Bioethics Committee of the Pontificia Universidad Católica de Chile, accredited by the Chilean Ministry of Health. Its approval number is 012793. This protocol has been registered in a ClinicalTrials.gov (accessed on 3 December 2023), a publicly accessible repository in accordance with the international standards set by the International Committee of Medical Journal Editors regarding the conduct of clinical trials. Its registration number is NCT06086990.

## 5. Conclusions

This study protocol outlines an innovative approach to address challenges in cancer care, specifically focusing on chemotherapy for various solid carcinomas. The *Contigo* app introduces a cutting-edge telemonitoring platform that could significantly improve the way in which follow-up is conducted amongst patients with cancer. This platform is designed to monitor chemotherapy toxicity symptoms and offer educational content to cancer patients.

The necessity for this tech-driven solution became apparent due to the limitations exposed by the COVID-19 pandemic of traditional follow-up approaches, underscoring the importance of remote monitoring in healthcare. *Contigo* strives to adopt a patient-centric approach by prioritizing patient experiences during chemotherapy. This is achieved through validated questionnaires and a multidisciplinary perspective. Among its potential clinical benefits is the generation of a novel remote monitoring alternative, aiming to alleviate the workload of oncology services by enabling the remote surveillance of patients. Additionally, this proposal has the potential to enhance the clinical monitoring process, increasing the detection rate of complications during treatment and improving assessment frequency by adapting to the patient’s needs. This platform also streamlines the utilization of validated tools for detecting symptoms and complications in oncology patients, potentially contributing to the enhancement of control quality and facilitating research development in the field.

The application comprises modules that encompass vital aspects of cancer care, allowing patients to report their health status and experiences, access educational materials, and connect with community resources. Notably, this study aims not only to improve the patient experience, but also to assess its impact on healthcare providers. This includes evaluating clinician satisfaction and its potential influence on patient care.

While the protocol outlines robust plans for data collection and statistical analysis, it acknowledges certain limitations such as sample size and specific cancer types being targeted. Its randomized design will mitigate the possibility of selection and confusion biases, and the use of validated questionnaires reduces the possibility of systematic errors due to information bias. Nevertheless, it lays the groundwork for a promising study that could significantly advance cancer care by leveraging technology to bridge gaps in patient monitoring and support.

## Figures and Tables

**Figure 1 mps-07-00024-f001:**
[figure not shown]
CONSORT flow diagram for the EQUALITE study.

**Figure 2 mps-07-00024-f002:**
[figure not shown]
Contigo application user interface.

## Data Availability

No new data are currently available for data sharing. However, upon completion of the trial, data will be made available to researchers upon reasonable request by contacting the authors.
